**Using Standards-based Audit to improve Maternal and New-born Health in Malawi - Study Protocol**

**Background**

The latest estimates on mortality show that almost 303,000 women die each year of pregnancy-related causes worldwide and that 99% of these occur in low and middle-income countries^1^. Furthermore, almost three million stillbirths and an estimated 2.6 million neonatal deaths occur per year, the latter accounting for at least 46% of deaths in children aged less than five years^2^. Most of these deaths could be prevented or avoided through actions that are proven to be effective and affordable.

Audits are proven to be effective to improve professional practice^3^ and recently, such audits have been given attention in the domain of obstetric care in low- and middle-income countries^4,5^ . Standard based audit (SBA) also known as criteria-based audit (CBA) is one a useful method which has been used to define and improve quality of care in maternal and newborn health among others (maternal and perinatal death audit and near miss audit)^6,7^. SBA is defined as quality improvement (QI) process that seeks to improve patient care and outcomes by systematically reviewing care against explicit standards, with identification and implementation of changes needed to achieve the desired standard of care^8^. The aim in conducting SBA- is to improve adherence to agreed standards.  If facilities maintain the practices adopted within the audit cycle it is anticipated that care will improve the clients of the facilities will benefit**.**

Recently the World health organisation (WHO) has developed standards for maternal and neonatal health as part of the WHO integrated management of pregnancy and childbirth care (IMPAC) package, which provides guidance for assisting countries to improve the health and survival of women and their newborn babies during pregnancy, childbirth, and the postnatal period^9^. WHO recommends countries to adapt the standards and streamline within national quality of care strategies and frameworks for the delivery of maternal and newborn health services to ensure that the services provided are of high quality.

A complete SBA cycle comprised of five steps: (i) establish a standard, (ii) measure practice, (iii) feedback findings and set standards, (iv) implement change, (v) re-evaluate practice and feedback findings. SBA provides an important insight into deficiencies in clinical practice and are routinely used as part of quality assurance efforts in industrialized countries but underutilized in low- and middle-income countries^10^. Reports of successfully completed cycles on the quality of delivery care are very scanty,

Malawi has achieved significant progress during the past decades in reducing maternal, newborn and child mortality. Child mortality was estimated at 64 per 1,000 live births in 2015, a remarkable progress from the levels registered in 1990 (250 per 1,000 live births). Despite this progress, 15,000 newborns still die in Malawi every year^11^. Maternal mortality was estimated at 957/100,000 live births in 1990 and at 634/100,000 live births in 2015^i^. Maternal deaths represent about 15% of all deaths of women in the reproductive age group (15-49 years), which translates to an estimated 3,400 pregnant women dying every year. With the transition from Millennium Development Goals to the new global Sustainable Development Goals, absolute targets have been set to reduce maternal deaths, stillbirth, and neonatal mortality^12^ and there is still more to be done. To maintain the gains made, and to achieve the global health targets for ending preventable maternal and newborn deaths^13,14^ , a new emphasis on improving quality of care at the time of birth, and for sick newborns, is required in Malawi.

The aim of this study is to assess the impact of using standards-based audit on compliance with defined standards for emergency obstetric and newborn care in Malawi

Study hypothesis:

In Malawi, SBA has been implemented before^4^, however, there is paucity in data to assess how health care providers comply to implement standards selected. Thus, our hypothesis is “Introducing the practice of conducting standards-based audits within facilities providing emergency obstetric and newborn care in Malawi will improve compliance to standards of care”.

# **Methods**

Study design:

A Cluster randomised incomplete stepped wedge trial for multiple standards on obstetric Care will be applied to assess the impact of using standards-based audit on compliance with defined standards for emergency obstetric and newborn care in Malawi. To appropriately reflect the diversity of expert opinion and disciplinary perspectives, a set of standards around emergency obstetric and newborn care were developed using a systematic, participatory process in accordance with WHO process of developing guidelines^15^ . The standards were mainly developed to address the common obstetric and newborn causes of death in low resource settings (cite). There are 25 standards in 7 groups (subsequently referred to as Standards Groups A, B, C, D, E, F and G) which have been defined (Appendix 1)

A total of 44 facilities are included in the design comprising of 10 designated to provide Comprehensive emergency obstetric care CEmOC and 34 facilities designated to provide basic emergency obstetric care (BEmOC) health facilities. Each participating facility is a cluster, and each facility will implement two periods of standards-based audit cycles. Each audit cycle comprises three months (a quarter): an assessment month, a month for action to address issues and a re-assessment month. Each of the ten CEmOC facilities will complete two standards-based audits in each quarter (four standards in total) and each of the 34 BEmOC facilities will complete one standards-based audits in each quarter (two standards in total).

Each standard assessed will be assessed using the incomplete stepped wedge design shown in Figure 1. Up to three facilities will be assigned to each sequence.

**Figure 1: Schematic representation of measurements of compliance with a single standard by sequence and month of study**

| Sequence | Stratum | Month | | | | | | | |
| --- | --- | --- | --- | --- | --- | --- | --- | --- | --- |
|  |  | July | Aug | Sept | Oct | Nov | Dec | Jan | Feb |
| 1 | I | 0 |  | 1 |  |  | 1 |  |  |
| 2 | II |  | 0 |  | 1 |  |  | 1 |  |
| 3 | III |  |  | 0 |  | 1 |  |  | 1 |
| 4 | I | 0 |  |  | 0 |  | 1 |  |  |
| 5 | II |  | 0 |  |  | 0 |  | 1 |  |
| 6 | III |  |  | 0 |  |  | 0 |  | 1 |

0 denotes assessment of compliance with the standard under the current standard of care.

1 denotes assessment of compliance after taking action to improve the quality-of-care delivery for the standard

**Condition**

Recipient of obstetric or new-born care.

**Intervention**

The intervention is the adoption by a healthcare facility of standards-based audits for standards of emergency obstetric and newborn care. Using the stepped wedge design each participating health care facility (cluster) acts as their own control, providing data for standards audited within the facility both prior to and subsequent to the action phase of the audit cycle.

**Trial setting**

Health care facilities

# **Study sites**

A total of 10 facilities designated to provide CEmOC and 34 facilities designated to provide BEmOC, from five districts in Malawi are to participate in the trial. The Table 1 below shows their distribution across the districts. Names of all facilities are in Appendix 2

**Table 1: Distribution of health facilities across the districts.**

| **District** | **CEmOCS** | **BEmOCs** |
| --- | --- | --- |
| Dedza | 2 | 8 |
| Blantyre | 2 | 7 |
| Thyolo | 2 | 6 |
| Mangochi | 2 | 9 |
| Nkhata Bay | 2 | 4 |
| **Total** | **10** | **34** |

**Primary outcome measure**

Compliance with defined standard of care aggregated for all emergency obstetric and newborn care standards audited. This will be defined as the mean across all facilities and standards, with each standard audited by each facility carrying equal weight. (Thus, at facility level the means for CEmOC facilities which audit twice as many standards will carry twice the weight of the BEmOC facilities). Standards will be weighted by the number of facilities which audit the standard).

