These calculations indicate that there will be at least 80% power to detect an improvement in compliance of 22% provided the ICC does not exceed 0.2 and the CAC does not fall below 0.5. If the initial compliance level is lower or higher than 50% then the difference detectable will be smaller. For standards that are audited in fewer clients per cluster or in fewer clusters the difference detectable will be larger. To indicate the impact of each of these reductions in sample size the differences detectable are also provided for 10 clients per cluster with 18 facilities and for 25 clients per cluster with 12 facilities auditing the standard.

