**Statistical Analysis**

Each standard considered will be analysed separately to provide an estimate of the impact of the audit of that standard on compliance with the standard. Analysis will use the binary responses of respondents within facilities in multilevel mixed effects logistic regression models, with fixed effects for intervention and facility type, and random effects for month, facility (cluster) and month by facility (cluster) interaction. District will also be considered for inclusion as a random effect. For each standard the impact of the intervention will be estimated with a 95% confidence interval. Compliance with defined standard of care, aggregated for all standards audited will also be estimated in a similar manner, with a 95% confidence interval.

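### The primary outcome is defined as an equally weighted mean compliance, but the planned pooled logistic model carries neither those weights nor a step back to that mean

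*Protocol*

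**What the plan says.** **Target.** Under Primary outcome measure, the protocol fixes both the summary and the weights: "This will be defined as the mean across all facilities and standards, with each standard audited by each facility carrying equal weight". It spells out two consequences: "at facility level the means for CEmOC facilities which audit twice as many standards will carry twice the weight of the BEmOC facilities" and "Standards will be weighted by the number of facilities which audit the standard". This is an arithmetic mean on the compliance scale.

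**Analysis.** Under Statistical Analysis, each standard is handled separately: "Analysis will use the binary responses of respondents within facilities in multilevel mixed effects logistic regression models". The fixed part holds the intervention and the type of facility; the other terms listed are "random effects for month, facility (cluster) and month by facility (cluster) interaction". The primary outcome gets one sentence: "Compliance with defined standard of care, aggregated for all standards audited will also be estimated in a similar manner, with a 95% confidence interval". The section does not say how the weights enter, how the different standards are represented in the pooled model, or on what scale the aggregate effect is reported.

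**Planning.** Sample size considerations works in percentage points and for a single standard: "at least 80% power to detect an improvement in compliance of 22" per cent, from an assumed initial compliance of 50%.

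**The concern.** A mixed logistic model on individual responses does not by itself give an equally weighted mean. Its intervention coefficient is a log odds ratio, conditional on the random effects. Each facility and standard contributes to it according to its information, which depends on how many clients it has, how close compliance is to 50%, and how strongly its observations are correlated. None of these is the weight in the outcome definition.

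If the coefficient is taken as the primary result, the trial reports an effect averaged over facilities and standards in proportions other than those declared. A single odds ratio also does not determine the change in mean compliance when standards start from different levels. What is at stake is the size and meaning of the primary estimate and its interval.

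**Working it through.** **1. The stated weights.** Pairs: 10 × 4 + 34 × 2 = 108, each weighing 1/108. A CEmOC facility has 4/108 and a BEmOC facility 2/108, a ratio of 2. The CEmOC share is 40/108 = 37%. (Eligibility gives 43 facilities and Target number of participants gives 33 BEmOC facilities, but the stated total of 8,100 fits 34: 10 × 300 + 34 × 150. With 33 there are 106 pairs, and the 2:1 ratio is unchanged.)

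**2. The planning figure.** For the Figure 1 design with 18 facilities, 25 clients, ICC 0.2 and CAC 0.5, the detectable difference solves d = (z for two-sided 0.05 + z for power) × SE. The SE comes from generalised least squares with categorical months, and the 0.05 level is assumed because none is stated. This gives 21.6 points at 80% power and 24.6 at 90%; Table 4 has 21.6 and 24.7. Planning was therefore on the absolute scale, for one standard.

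**3. Weight by facility type if the plan is met exactly.** Assumptions:
- a linear mixed model as an approximation to the logistic one;
- categorical months and a facility-type term;
- facility and facility-month effects shared across standards, as the analysis section is worded;
- 25 clients in every cell and the Figure 1 schedule;
- CEmOC facilities split 3/3/4 and BEmOC 11/12/11 over strata. (Randomisation says 2 or 3 CEmOC facilities per stratum, which totals at most 9, so one stratum must take a fourth.)

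The reason can be seen by hand. The mean of k standards in one facility-month has variance ICC(1 − CAC) + (1 − ICC)/(25k), apart from the facility effect. At ICC 0.2 and CAC 0.5, going from one standard to two changes it from 0.1 + 0.032 = 0.132 to 0.1 + 0.016 = 0.116. Doubling the standards multiplies the information by 0.132/0.116 = 1.14, not 2. At ICC 0.1 and CAC 0.8 the factor is 0.056/0.038 = 1.47.

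The full calculation takes the coefficients that form the estimated intervention effect, sums them over intervention cells by facility type, and divides by the number of facilities:

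| ICC | CAC | CEmOC : BEmOC weight per facility | CEmOC share |
|---|---|---|---|
| 0.1 | 0.8 | 1.44 | 30% |
| 0.1 | 0.5 | 1.25 | 27% |
| 0.2 | 0.8 | 1.26 | 27% |
| 0.2 | 0.5 | 1.13 | 25% |
| Stated outcome | | 2.00 | 37% |

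Moving the fourth CEmOC facility to another stratum changes the range only to 1.11–1.45.

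**4. What that shift is worth.** If the true effect differed by an assumed 10 points between facility types, the estimate would move by (0.370 − 0.298) × 10 = 0.7 to (0.370 − 0.250) × 10 = 1.2 points. This is modest, but it is not the declared quantity.

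**5. Weight by baseline, on assumed rates.** Take two equal sets of pairs with 25 clients per cell: set A moves from 50% to 72%, set B from 90% to 95%. The stated outcome is (22 + 5)/2 = +13.5 points, weighted 50/50. On the logit scale, the variance of a pair's log odds ratio is 2τ² + 1/(n·p₀(1 − p₀)) + 1/(n·p₁(1 − p₁)), with τ² = ICC(1 − CAC)/(1 − ICC) × π²/3. At ICC 0.2 and CAC 0.5, τ² = 0.411:
- A: 0.822 + 0.160 + 0.198 = 1.18
- B: 0.822 + 0.444 + 0.842 = 2.11
- A's weight: 2.11/(1.18 + 2.11) = 64%

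Over the protocol's ICC and CAC values, A takes 64% to 74%. The weighted odds ratio is 2.40 to 2.44, against 2.33 with equal weights on the log scale. If B does not change (90% to 90%), the equal-weight difference is +11.0 points, A takes 59% to 67%, and the odds ratio is 1.75 to 1.89 against 1.60. If B (90% to 95%) has only 10 clients per cell, A takes 77% to 87%. This illustrates the weighting; it is not a full model fit.

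**6. Scale, on assumed baselines.** A common odds ratio of 2.5 is +21 points from 50%, +11 from 80%, +6 from 90% and +3 from 95%.

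**The case against.** **The odds ratio is inferred.** The protocol never says that the primary result will be an odds ratio. It says aggregated compliance will be estimated, and predicted mean compliance is a routine output of a mixed logistic model. This stands: one cannot say the protocol commits itself to a conditional odds ratio, only that this is the model's natural effect estimate and that no other step is given.

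**Post-estimation belongs in a SAP.** This stands in part. Silence on reporting scale alone would be no finding. Here, however, the protocol itself fixes the weights and names a model that does not apply them, so the two sections need to be joined.

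**The fixed 25 clients per cell already supply the weights.** CEmOC facilities do contribute twice the data. If every facility-standard pair had its own independent random effects, the ratio would be about 2. But the effects named are for facility and month by facility, shared across standards, so twice the data does not bring twice the weight.

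**The illustrations rest on chosen inputs.** True. The only baseline in the protocol is 50%, and 10 clients per cell is a sensitivity row in Table 4. In the two-set examples the direction of effect agrees under either weighting, and with effects in both sets the odds ratios differ by only 3% to 5%.

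**Table 4 concerns single standards.** Correct. A reader might infer that the primary result could not be compared with its own planning difference, but the protocol states no planning difference for the aggregate. Table 4 belongs to the secondary outcome.

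**Conclusion.** The primary outcome and its analysis do not match as written. The definition requires each of the 108 facility-standard pairs to count equally. The pooled model, followed as described, gives a CEmOC facility about 1.1 to 1.4 times a BEmOC facility's weight instead of 2, and favours standards with mid-range compliance. The ratio rests on a linear approximation, shared facility and facility-month effects, and full recruitment of 25 clients per cell.

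The consequence depends on heterogeneity: effects that differ by facility type or standard, or unequal baselines or cell sizes. The protocol gives no values for these. A reader might infer that the trial could reach a false conclusion about whether audit works. The document does not support that: if no standard has an effect, both targets are null, and the examples do not reverse direction. Nor does any change to the sample size follow. The problem is that the primary estimate would not be the quantity declared. This should be fixed before analysis; confidence is moderate.

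**What to change.** In Statistical Analysis, state how the aggregate is obtained:

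1. Fit the pooled model with terms for standard, intervention by standard and intervention by facility type, or apply explicit equal weights per cell.
2. Predict compliance for every audited facility-standard pair with the intervention off and on.
3. Average over pairs with equal weight, as the outcome definition requires.
4. Report the difference in mean compliance in percentage points with a 95% interval (for example by bootstrap over facilities) as the primary result, with the odds ratio as supportive.

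The interaction terms or weights in step 1 are needed. In a simplified fixed-effects logistic check with one common intervention effect, averaging predictions returned the target exactly at 25 clients per cell (+13.5 and +11.0 points). When a set with no effect had 10 clients per cell, it gave +13.1 against a target of +11.0.

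The alternative is to redefine the primary outcome as the model's own effect measure and drop the stated weights.

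The cost is wording, a little more analysis work and possibly a slightly wider interval. No new data are needed and the design does not change.

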**Secondary outcome measure**

Compliance with defined standard of care for each of the emergency obstetric and newborn care standards audited in the study.

**Randomisation**

Facilities have been randomised to three strata of 14 or 15 facilities, with each stratum including 2 or 3 CEmOC facilities. The stratum assigned determines the month in which the first audit cycle will be commenced (July, August, and September) in the facility. Randomisation was done using a Stata program using the runiform function. The randomisation was as balanced as possible within districts and facility type.

Three training workshops will be conducted for health care providers from each participating facility, before commencing the first audit cycle. There will be three workshops, one for health care providers in each stratum. During these workshops staff will be trained in the conduct of standard based audits. During the workshop they will also identify standards of most relevance to their facility which can be audited. Staff from each CEmOC facility will be asked to select 6 such standards for which the facility usually has at least 25 clients per month. Staff from BEmOC facilities will be asked to select 4 standards. They will rank these standards in terms of their importance to the facility.

The trial statistician will then assign standards to be audited within each facility in a manner which assigns the highest-ranking standards for each facility subject to the number in the stratum not exceeding six facilities for any given standard. In determining the standards to be audited at each facility priority will be given to the more popular standards, to maximise the number of individual standards for which there are close to 18 facilities auditing the standard following a balanced incomplete stepped wedge design.

The sequence in which standards are audited within each facility will be assigned using a Stata program using the runiform() function to randomise the facilities to quarters (1 or 2) for each standard. The allocation will be constrained to ensure that for each facility the appropriate number of standards are assigned to each quarter.

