**Sample size considerations**

For sample size calculations various parameters need to be specified. These include the intracluster correlation (ICC) and the cluster autocorrelation (CAC). The ICC refers to the correlation between values from individuals in the same cluster on the same occasion. The CAC measures the correlation between means within the same cluster at different times. It is assumed that data for each standard are collected according to the incomplete stepped wedge design shown in Figure 1, with three clusters following each sequence in the design. Sample size calculations were performed to determine differences detectable using the Rshiny app which was developed by [name], a Professor of Biostatistics whose research is focused on the design and analysis of stepped wedge trials (available at: <https://clusterrcts.shinyapps.io/rshinyapp/>).

Table 4 indicates the percentage change in compliance for the standard that is detectable for a single standard, with either 80% or 90% power, an ICC of either 0.1 or 0.2, and a CAC of 0.8 or 0.5 using a sample of 25 clients for each assessment month in each cluster. These calculations focused on the proportion of respondents who deemed the standard to have been achieved as a binary response, assuming that the initial compliance level for the standard is 50%.

**Table 4 Differences detectable (percentage) for using an incomplete stepped wedge design with specified number of facilities conducting a standards-based audit in a balanced incomplete stepped wedge design**

| **Sample size for each facility-month** | **Number of facilities doing standards-based audit** | **ICC** | **CAC** | **Power** | |
| --- | --- | --- | --- | --- | --- |
|  |  |  |  | **80%** | **90%** |
| 25 | 12 | 0.1 | 0.5 | 21.1% | 24.0% |
|  |  |  | 0.8 | 18.3% | 20.9% |
|  |  | 0.2 | 0.5 | 26.0% | 29.3% |
|  |  |  | 0.8 | 20.9% | 23.9% |
| 25 | 18 | 0.1 | 0.5 | 17.5% | 20.0% |
|  |  |  | 0.8 | 15.2% | 17.5% |
|  |  | 0.2 | 0.5 | 21.6% | 24.7% |
|  |  |  | 0.8 | 17.5% | 20.0% |
| 10 | 18 | 0.1 | 0.5 | 21.7% | 24.7% |
|  |  |  | 0.8 | 20.5% | 23.5% |
|  |  | 0.2 | 0.5 | 25.6% | 28.9% |
|  |  |  | 0.8 | 23.0% | 26.1% |

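### The rule assigning standards to facilities sets a ceiling per stratum but no floor, so a less popular standard can lose much or all of its concurrent control

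*Protocol*

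**What the plan says.** - Protocol, Randomisation: facilities are randomised to three strata of 14 or 15, which fix the month in which auditing starts. Staff list and rank standards at training workshops: "There will be three workshops, one for health care providers in each stratum". CEmOC facilities list six standards and audit four; BEmOC facilities list four and audit two.
- The statistician then assigns the highest-ranked standards "subject to the number in the stratum not exceeding six facilities for any given standard". Popular standards take priority, "to maximise the number of individual standards for which there are close to 18 facilities auditing the standard following a balanced incomplete stepped wedge design". No minimum per stratum is given.
- The later draw of quarters is restricted within facilities only: "The allocation will be constrained to ensure that for each facility the appropriate number of standards are assigned to each quarter".
- Methods: "Up to three facilities will be assigned to each sequence".
- Sample size considerations: "It is assumed that data for each standard are collected according to the incomplete stepped wedge design shown in Figure 1". The main calculation puts three facilities on each of the six sequences, 3×6 = 18 in all. The caption of Table 4 limits it to a balanced design. The text after the table also offers figures "for 25 clients per cluster with 12 facilities auditing the standard", and warns that fewer clusters or clients raise the detectable difference. It does not mention an uneven spread over strata.
- Secondary outcome measure and Statistical Analysis: each audited standard is an outcome and receives its own intervention estimate with a 95% confidence interval.

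**The concern.** A stepped wedge design earns its control from months in which some clusters have switched and others have not. Figure 1 supplies such months only between strata, so a standard's spread over strata decides whether its estimate is controlled at all. The assignment rule limits how many facilities a stratum may contribute but does not require any to come from it. The quarter draw cannot repair this, because moving a facility between quarters never creates a month with both conditions inside one stratum. At stake are the separate estimates for less popular standards: their precision, and whether they can be told apart from a secular change in compliance.

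**Working it through.** **1. Where the controls come from (Figure 1).** Within stratum I the readings are July 0, Sept 1, Oct 0, Dec 1. Strata II and III repeat this one and two months later. No month within a stratum holds both a 0 and a 1. Months with both conditions across strata:

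| Month | Intervention | Control |
|---|---|---|
| Sept | I | III |
| Oct | II | I |
| Nov | III | II |
| Dec | I | III |

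All three strata give four such months, I+III two, I+II one, II+III one, and a single stratum none.

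**2. Which standards are exposed.** Under a cap of six, two strata hold at most 12 facilities. A standard with 13 or more cannot miss a stratum, and 18 must be 6/6/6. There are 10×4 + 34×2 = 108 facility-standard slots (106 with the 33 BEmOC facilities given under Target number of participants). This is at most 108/18 = 6 full standards, out of 25 defined. Only standards with 12 or fewer facilities are at risk.

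**3. Reproducing Table 4.** Inputs from the protocol: Figure 1 cells, 25 clients, ICC 0.1 or 0.2, CAC 0.5 or 0.8, 50% initial compliance. Assumed: two-sided 5% (inferred from the 95% interval), fixed month effects, quarters split evenly.

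The variance v of the effect, per unit of total variance, comes from generalised least squares on facility-month means. Its components are facility ICC×CAC, facility-month ICC×(1−CAC) and residual (1−ICC)/25. The total variance is the average of p(1−p) under the two conditions, 0.25 − d²/2. The detectable difference solves d = (1.960 + 0.842)·√[v(0.25 − d²/2)]. With k² = 7.849v this gives d² = 0.25k²/(1 + k²/2).

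For ICC 0.1 and CAC 0.5:
- 4/4/4: v = 0.0247, k² = 0.194, d = 21.0 points (Table 4: 21.1)
- 6/0/6: v = 0.0401, k² = 0.315, d = 26.1
- 6/6/0: v = 0.0817, k² = 0.641, d = 34.8

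**4. Same 12 facilities, different spread (points detectable, 80% power).**

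| Spread I/II/III | 0.1/0.5 | 0.1/0.8 | 0.2/0.5 | 0.2/0.8 |
|---|---|---|---|---|
| Table 4 | 21.1 | 18.3 | 26.0 | 20.9 |
| 4/4/4 | 21.0 | 18.2 | 25.9 | 20.9 |
| 6/4/2 | 22.6 | 19.6 | 27.7 | 22.4 |
| 6/0/6 | 26.1 | 26.7 | 32.8 | 33.5 |
| 6/6/0 or 0/6/6 | 34.8 | 33.0 | 41.6 | 39.0 |

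Columns are ICC/CAC. At Table 4's own 80% differences, power falls to 36–60% for 6/0/6 and 26–34% for 6/6/0. With one stratum (at most six facilities) the design matrix is rank deficient: the effect cannot be separated from month.

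**5. The planned model.** Statistical Analysis specifies random, not fixed, month effects, and no month variance is given. For ICC 0.1 and CAC 0.5 at 80% power, with the month variance as an assumed share of the total:

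| Spread | 0 | 0.01 | 0.05 |
|---|---|---|---|
| 12, balanced | 13.9 | 15.3 | 17.7 |
| 12, strata I+III | 13.9 | 15.8 | 19.4 |
| 12, strata I+II | 13.9 | 16.8 | 22.5 |
| 6, balanced | 19.3 | 20.4 | 22.8 |
| 6, one stratum | 19.3 | 23.6 | 33.5 |

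The one-stratum estimate becomes computable, but only from before-after change with month effects shrunk towards zero.

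**6. How often a stratum is missed.** Assumption: the facilities auditing a standard are a random draw from strata of 14/15/15.
- 6 facilities: [C(30,6) + 2C(29,6) − C(14,6) − 2C(15,6)]/C(44,6) = (593,775 + 950,040 − 3,003 − 10,010)/7,059,052 = 22%
- 4 facilities: (27,405 + 47,502 − 1,001 − 2,730)/135,751 = 52%
- 12 facilities under the cap (only 6/6/0 in some order): about 0.3%

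A single-stratum outcome is rare: 13,013/7,059,052 = 0.2% with six facilities, 3,731/135,751 = 2.7% with four.

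**The case against.** The strongest reply is that the rule already aims at balance. With priority to popular standards and a cap of six, those that reach about 18 facilities are evenly spread by construction. This stands, and it confines the point to the leftover standards.

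A reader might infer that Table 4 is wrong. It is not: its 12-facility figures reproduce, and its caption states the balanced condition. What is missing is a rule that secures the condition for smaller standards.

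A reader might also take 6/6/0 as a likely outcome, or set these losses against the protocol's 22-point statement. Neither is supported. Under random spread 6/6/0 is very rare, and 22 points is the claim for 18 facilities; Table 4 itself gives 26.0 for 12 at ICC 0.2 and CAC 0.5. Separate workshops might make choices differ between strata, but nothing in the protocol shows this, and randomisation balanced within district and facility type argues against it.

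The planned random-month model softens the loss of precision to a degree that the protocol does not let us compute. This also stands. It does not restore concurrent control, which depends on the layout and not on the model.

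Finally, a reader might infer damage to the primary outcome. The pooled estimate draws on all three strata, and no harm to it has been shown. How sparse standards are reported may also be left to the analysis plan, but assignment happens before data collection and no analysis can supply controls that were never observed.

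**Conclusion.** The point holds for standards audited by 12 or fewer facilities, and matters mainly for those with about six or fewer. For these the written rule allows a separate estimate that rests largely or wholly on before-after change. The losses in detectable difference (from 18.2–25.9 points to 26.1–33.5 or 33.0–41.6 with 12 facilities) rest on fixed months, an even quarter split and two-sided 5%. The frequencies (0.3%, 22% and 52% for 12, 6 and 4 facilities) rest on random spread over strata of 14/15/15. An uneven spread that still uses all three strata costs little: 6/4/2 adds 1.4 to 1.8 points. The matter touches the secondary outcome only, and is a cheap improvement, not a flaw in the trial's main comparison.

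**What to change.** In Randomisation, add to the cap: where the facilities' ranked lists allow, each audited standard is assigned in all three strata, in numbers as equal as possible and with at least two facilities per stratum. The spare choices already collected (six listed for four audits, four listed for two) give the room to do this.

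Where it cannot be met, which includes any standard with fewer than 2×3 = 6 facilities, report that standard's separate result as an uncontrolled or weakly controlled before-after change, and keep it in the pooled analysis.

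In the text after Table 4, say that the 12-facility figures hold only for an even spread over the strata.

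The cost is one more constraint in the assignment step and a few sentences. The downside is that some facilities will audit a lower-ranked standard from their own list.
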